### **3.3.2. Control Group**

The control group will also perform the exercises using the Orygen Dual Valve® (Forumed S.L., Girona, Spain) device. A sham intervention will be implemented: the initial resistance of the device will be 0cmH2O, and will be maintained throughout the intervention period - there will be no load progression. All procedures adopted with the experimental group, including the weekly home visit, will also be performed with individuals in the control group. However, there will be no real change in the training load. All devices will be wrapped with an opaque material so that the load or possible respiratory training load is not visualized.

### **3.4. Outcome measurements**

Outcome measurements will be performed at baseline (week 0), immediately after training (week 8), and one month after training (week 12). In the initial evaluation, clinical and demographic data of all individuals, identification, and characterization of the sample

will be collected.

In all three evaluations, measurements of MIP and MEP, inspiratory muscle endurance, peak cough flow, dyspnea, fatigue, exercise capacity, and quality of life will be performed. An examiner, blinded to the group allocation, will perform all these measurements. All participants will be instructed not to comment on information about the training received.

### **3.5. Instruments**

#### **3.5.1. Primary Outcomes**

##### **3.5.1.1. Inspiratory Muscle Strength**

Inspiratory muscle strength will be measured using MIP. Measurements will be performed using a digital manovacuometer (NEPEB-LabCare/UFMG, Brazil) and reported in cmH2O (PESSOA et al., 2014; PESSOA et al., 2015). The determination of the manovacuometer variables is performed using the MANOVAC 4.0 software. The manovacuometer is the gold standard instrument to measure respiratory muscle strength (PESSOA et al., 2014). Individuals will perform inspirations against an obstructed airway within the mouthpiece. The collection will be performed with the individual sitting in a chair, with the feet and back supported and the torso at a 90-degree angle with the hip. A conventional mouthpiece and nose clip will be used (PESSOA et al., 2015). Individuals will be instructed to breathe comfortably two to three times at tidal volume level. Five acceptable measurements will be taken. The highest pressure of three reproducible measurements, with less than 10% variability, will be recorded and used for analysis (PESSOA et al., 2015).

##### **3.5.1.2. Expiratory Muscle Strength**

Expiratory muscle strength will be measured using MEP. MEP will be measured with the same digital manovacuometer (NEPEB-LabCare/UFGM, Brazil), and reported in cmH2O (PESSOA et al., 2014; PESSOA et al., 2015). To record expiratory pressures, individuals will perform expirations against an obstructed airway within the mouthpiece (PESSOA et al., 2015). The collection protocol will be the same as previously described for the evaluation of inspiratory muscle strength. The highest pressure of three reproducible measurements, with less than 10% variability, will be recorded and used in data analysis (PESSOA et al., 2015).

### **3.5.2. Secondary Outcomes**

#### **3.5.2.1. Inspiratory Muscle Endurance**

The number of breaths that the individual can perform will measure inspiratory muscle endurance. Individuals will be instructed to breathe against a submaximal inspiratory load (50% of maximal inspiratory pressure), until fatigue or up to the seven-minute limit (CHARUSUSIN et al., 2013). The POWERbreathe® KH1 instrument will be used, and the recommendations for using the equipment will be followed (CHARUSUSIN et al., 2013). The total number of repetitions will be used for analysis (CHARUSUSIN et al., 2013).

#### **3.5.2.2. Peak Cough Flow**

The peak cough flow measurements will be performed with the peak expiratory flow meter (Mini-Wright Peak Expiratory Flow Meter) (FREITAS et al., 2010). For that, the individual must take a deep breath (total lung capacity), and then cough as vigorously as possible (BACH et al., 2006). At least three measurements will be performed that must have a different maximum of 5% between them (FREITAS et al., 2010; PEREIRA et al.,

2002). The highest value, in L/min, will be recorded and used in the analyzes (FREITAS et al., 2010; PEREIRA et al., 2002).

#### **3.5.2.3. Dyspnea**

Dyspnea will be measured using the Medical Research Council (MRC) instrument (KOVELIS et al., 2008). The participants will be asked to choose which level best represents how dyspnea limits their activities of daily living on a 5-point scale, in which 0 indicates 'breathless only with strenuous exercise' and 4 indicates 'too breathless to leave the house'. (KOVELIS et al., 2008). This measurement tool has adequate measurement properties for evaluating dyspnea in this population (KOVELIS et al., 2008). The total score will be used in the analyses.

#### **3.5.2.4. Fatigue**

Fatigue will be measured using the Fatigue Severity Scale (FSS). This instrument measures the impact of fatigue on activities of daily living. Nine statements compose this instrument, and participants will be asked to rate how much they agree with each of the statements. For each item, the score ranges from 1 to 7, where 1 completely disagrees and 7 completely agrees. The FSS is recommended for evaluating fatigue in individuals with PD (FRIEDMAN et al., 2010) and has adequate measurement properties for measuring fatigue in this population (FRIEDMAN et al., 2010; VALDERRAMAS et al., 2012). The total score will be used in the analyzes

#### **3.5.2.5. Exercise Capacity**

Exercise capacity will be measured using the six-minute walk test (6MWT) (BLOEM et al., 2016; STEFFEN et al., 2008). The 6MWT will be performed in a 30-meter hallway, delimited by two cones. Individuals will be instructed to walk as far as

possible in six minutes, and standardized stimuli will be provided every minute of the test. Two tests will be performed with an interval of 30 minutes between them, according to the guidelines of the European Respiratory Society / American Thoracic Society (HOLLAND et al., 2014). The test with the greatest distance (in meters) walked will be considered and used in the analyses (HOLLAND et al., 2014).

#### **3.5.2.6. Quality of Life**

Quality of life will be measured using the Parkinson's Disease Questionnaire-39 (PDQ-39) (JENKINSON et al., 1997). This instrument consists of 39 items, divided into eight dimensions. For each item, there are five response options, and scores range from 0 (never) to 4 (always or it is impossible for me) (JENKINSON et al., 1997). The score for each domain ranges from 0 (zero) to 100 (one hundred), where zero means better and 100 means the worse quality of life (JENKINSON et al., 1997). The PDQ-39 has adequate measurement properties for measuring fatigue in this population (LANA et al., 2007). The total score will be used for the analysis.

#### **3.6. Sample size calculation**

The sample size calculation was performed considering the primary outcome measures (inspiratory and expiratory muscle strength). The effect size for inspiratory muscle training was derived from an RCT with a similar population and intervention. Considering a significance level ( $\alpha$ ) of 5% and a power of 0.80, thirteen participants per group are required (26 participants). The effect size for expiratory muscle training was also derived from an RCT with a similar population and intervention. Considering a significance level ( $\alpha$ ) of 5% and a power of 0.80, fourteen participants per group are required (28 participants). Therefore, a sample size of 28 individuals (14 in each group)

was defined (the largest sample size calculated). Assuming an expected dropout rate of 20%, a total sample size of 34 individuals was set (17 in each group).

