**Belo Horizonte**

**Universidade Federal de Minas Gerais**

**School of Physical Education, Physiotherapy, and Occupational Therapy**

**2021**

## **ABSTRACT:**

**Background:** Individuals with PD commonly have a significant reduction in respiratory muscle strength and inspiratory muscle endurance, and it can intensify with the disease progression. Respiratory muscle training has been shown to increase respiratory muscle strength in individuals with Parkinson's disease (PD). However, the effect size on other functional outcomes has not been determined and/or investigated. In addition, studies investigating the effects of high-intensity respiratory muscle training (inspiratory and expiratory) in this population were not found.

**Objectives:** To investigate the efficacy of high-intensity respiratory muscle training (combined inspiratory and expiratory muscle training) in improving inspiratory and expiratory muscle strength, inspiratory muscle endurance, peak cough flow, dyspnea, fatigue, exercise capacity, and quality of life in this population.

**Design:** A randomized controlled trial with blinded evaluation will assign eligible participants to either high-intensity respiratory muscle training (experimental group) or sham training (control group). Individuals will perform a home-based intervention, not directly supervised, consisting of two daily 20-min sessions (morning and afternoon), seven times a week, during eight weeks. Study Outcomes: Primary outcomes are inspiratory and expiratory muscle strength. Secondary outcomes are respiratory muscle endurance, peak cough flow, dyspnea, fatigue, exercise capacity, and quality of life. The outcomes will be measured at baseline, post-intervention (after the 8-week intervention), and one month after the cessation of the intervention (12-week follow-up), by trained evaluators.

**Conclusion:** The results of this trial will provide valuable new information on the effects of high-intensity respiratory muscle training in improving muscle strength and other

functional outcomes in individuals with PD.

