### **3.7. Statistical analyzes**

All statistical analyzes will be performed by an independent examiner, blinded to the group allocation. Each participant will be assigned with a unique code. All analyses will be performed using SPSS (SPSS Inc., Chicago, IL, USA). The normality of data distribution will be verified for all continuous numeric variables. Descriptive statistics will be calculated for all outcomes. The effects of the interventions will be analyzed from the collected data using intention-to-treat. Data from the last available evaluation will be used for missed sessions. Two-way ANOVA with repeated measures (2\*3) will be used to evaluate the differences between groups, considering the time factor (considering baseline, post-intervention, and 4-week follow-up), for the variables: inspiratory and expiratory muscle strength, respiratory muscle endurance, peak cough flow, and exercise capacity. The level of significance will be set at 5% and adjusted for multiple comparisons. Data distribution and equality of variance will also be analyzed, to ensure the parametric analysis has been applied correctly. The effect sizes will be calculated to determine the magnitude of the differences between the groups. The differences between the two mean values will be expressed in units of their SD, expressed as Cohen's d, or mean results for the experimental group minus the mean results for the control group, divided by the SD of the control group. Effect sizes between 0.2 and 0.5 will be considered small; between 0.5 and 0.8, medium; and above 0.8, large.

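### Section 3.6 sizes each of two primary outcomes at an unadjusted 5%, section 3.7 tests at an adjusted level without naming the family, and no rule says whether one or both must succeed

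*Protocol*

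**What the plan says.** The abstract names two primary outcomes: "Primary outcomes are inspiratory and expiratory muscle strength". Section 3.6 confirms that both drive the sample size: "The sample size calculation was performed considering the primary outcome measures (inspiratory and expiratory muscle strength".

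Each outcome is then sized separately. For inspiratory strength the calculation is at a significance level "of 5% and a power of 0.80, thirteen participants per group are required (26 participants"; for expiratory strength it is at a level "of 5% and a power of 0.80, fourteen participants per group are required (28 participants". The two are combined by keeping the bigger one: 28 in total "was defined (the largest sample size calculated". Section 3.6 then enrols 17 per group to allow for 20% dropout. It mentions no split of alpha and no joint power.

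Section 3.7 plans a repeated-measures ANOVA with two groups and three visits for five outcomes, including both primaries, and states: "The level of significance will be set at 5% and adjusted for multiple comparisons". It names neither the method nor the set of comparisons. No section says whether the trial succeeds on one primary outcome or needs both, or which visit decides.

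**The concern.** The level at which the trial is sized may not be the level at which it is tested. If the adjustment in 3.7 reaches the two primaries, the 5% in 3.6 is not the operative level and the power of 0.80 does not carry over. If it covers only comparisons between visits, each primary is tested at 5%. The question is then whether either can count as success or both must.

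A result that is significant for MIP but not MEP, or the reverse, is quite possible. The present text would let it be reported as a success or as a failure, and the choice could be made after the p-values are known. Blinding the analyst to allocation, as 3.7 plans, does not prevent that.

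**Working it through.** **Inputs from section 3.6.** Alpha 5%, power 0.80, 13 per group (MIP) and 14 per group (MEP), 17 per group enrolled. The effect sizes come from earlier trials ("The effect size for inspiratory muscle training was derived from an RCT with a similar population and intervention"; "The effect size for expiratory muscle training was also derived from an RCT with a similar population and intervention") but no value is printed. The figures 13 and 14 therefore cannot be reproduced from stated inputs, only inverted.

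**Assumptions.** Two-sided two-sample t-test, equal groups. Sidedness is not stated, so one-sided is also tried below.

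**Formula.** With df = 2n − 2 and noncentrality δ = d√(n/2), power = P(|T| > t at 1 − α/2), with T noncentral t.

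**Step 1: back-solve d.** Because n is rounded up, each n fits a range. The lower end gives exactly 0.80 at the stated n; the upper end would give 0.80 with one fewer per group.
- MIP, n = 13: d = 1.145 to 1.197.
- MEP, n = 14: d = 1.100 to 1.145.

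Check: MEP at n = 14 and d = 1.100 has δ = 1.100 × √7 = 2.91, and the power at 5% is 0.80, as stated.

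**Step 2: power per outcome** (range over d).

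| Evaluable per group | Level | MEP | MIP |
|---|---|---|---|
| 14 | 5% | 0.80–0.83 | 0.83–0.86 |
| 14 | 2.5% (Bonferroni over two) | 0.70–0.74 | 0.74–0.78 |
| 17 | 2.5% | 0.80–0.83 | 0.83–0.87 |

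On a one-sided reading, halving alpha gives 0.69–0.72 for MEP at 14 per group, so sidedness hardly matters.

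**Step 3: Holm instead of Bonferroni, 14 per group.** With independent tests, power for one outcome = P(p < 0.025) + P(0.025 ≤ p < 0.05) × P(the other has p < 0.025).
- Lower-end d: MEP 0.701 + (0.800 − 0.701) × 0.739 = 0.774; MIP 0.739 + (0.831 − 0.739) × 0.701 = 0.803.
- Upper-end d: MEP 0.739 + (0.831 − 0.739) × 0.779 = 0.811; MIP 0.779 + (0.862 − 0.779) × 0.739 = 0.840.

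Simulation at the lower-end d, for correlations 0 to 0.8, gives about 0.76–0.77 (MEP) and 0.78–0.80 (MIP).

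**Step 4: both required, each at 5%, 14 per group.**
- Independent, lower-end d: 0.831 × 0.800 = 0.665. Upper-end d: 0.862 × 0.831 = 0.716.
- Correlations 0 to 0.8: 0.66–0.75 (lower-end d) and 0.72–0.79 (upper-end d).

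**Step 5: either suffices, 14 per group.**
- Each at 2.5%, independent, lower-end d: 1 − (1 − 0.739)(1 − 0.701) = 0.922, falling to 0.81 at correlation 0.8. Familywise error is at most 5%.
- Each at an unadjusted 5%: familywise error 1 − 0.95² = 0.0975 if independent, and a little over 8% at correlation 0.7.

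**Step 6: baseline adjustment at 2.5%, 14 per group.** With a baseline to week-8 correlation r, the effective effect is d/√(1 − r²), with one fewer df. Taking r = 0.5 (an assumption), √0.75 = 0.866. MEP becomes 1.100/0.866 = 1.270, power 0.83. MIP becomes 1.145/0.866 = 1.322, power 0.86. This treats the back-solved d as being in units of the week-8 SD.

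**The case against.** A reader might infer that no interpretation of the protocol gives 0.80 power with 5% error, or that the trial is simply underpowered. The document does not support either.

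- If either primary may succeed and each is tested at 2.5%, the chance of at least one success is 0.81–0.92 at the lower-end d, with familywise error at or below 5%.
- If the adjustment in 3.7 covers only comparisons between visits, the 0.80 per outcome in 3.6 is correct as stated. Section 3.6 makes no claim about joint power.
- The intention-to-treat analysis with the last evaluation carried forward could bring all 17 per group into the test. At 17, power at 2.5% is about 0.80–0.87 across the two outcomes, and power for both at 5% each is 0.79–0.84 at the lower-end d for correlations 0 to 0.8.
- Under Holm at the upper-end d there is no shortfall if the tests are independent (0.81 and 0.84).

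All four points stand. The figure for 17 per group is an upper bound: it spends the dropout allowance, and carried-forward baseline values would dilute the effect.

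Two further objections have some force. The planned test is a repeated-measures ANOVA, so a t-test is only a stand-in for it. And the adjustment method is commonly left to the statistical analysis plan. That does not dispose of the point. Section 3.6 has already fixed a level and a power, and whether they match the test depends on a family and a success rule that the protocol leaves open. A later document can name the rule, but the sample-size justification in 3.6 would still have to be checked against it.

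**Conclusion.** The mismatch between 3.6 and 3.7 is real, and the missing success rule is its more serious part. The per-outcome power of 0.80 is right only if each primary is tested at 5%. In that case familywise error is up to about 9.8% under an either rule, or joint power is about 0.66–0.75 under a both rule at the lower-end d (up to 0.79 at the upper end).

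If the adjustment covers the two primaries, per-outcome power at 14 evaluable per group is about 0.70–0.74 (MEP) and 0.74–0.78 (MIP) with Bonferroni. With Holm it is about 0.76–0.77 and 0.78–0.80 at the lower-end d.

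The direction of the error depends on the rule that is absent, so the conclusion is that the stated power cannot be tied to a defined test, not that it is too low in every case. The magnitudes rest on back-solved effect sizes, a two-sided t-test and assumed correlations; the inconsistency in the text does not.

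**What to change.** In 3.7, name the two primary tests as the baseline-adjusted group differences in MIP and MEP at week 8, and make other visits and outcomes secondary. Then state one success rule:

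- Holm across the two at 5% overall, with a claim allowed for each outcome that passes; or
- both must be significant, each tested at 5% with no adjustment.

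In 3.6, print the effect sizes and sidedness, and restate power under the chosen rule with its assumptions. Without baseline adjustment, the back-solved lower-end values would be about 0.76–0.77 (MEP) and 0.78–0.80 (MIP) for Holm, or 0.66–0.75 jointly if both are required. With baseline adjustment and r = 0.5, power is about 0.83 and 0.86 even at 2.5%; r should be justified or shown as a range.

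The cost is a few sentences in two sections, and a less favourable stated power if baseline adjustment is not adopted. Baseline is already measured, and no patients are added.

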## **3.0.METHODS**

A prospective, superiority parallel-group randomized controlled trial, with concealed allocation, allocation ratio 1:1, blinded evaluations, and intention-to-treat analysis will be carried out at the Department of Physiotherapy, Universidade Federal de Minas Gerais (UFMG).

The project will be submitted to the Research Ethics Committee of the Universidade Federal de Minas Gerais. All consents for the development of the study were obtained. This trial will be registered at [www.ClinicalTrials.gov](http://www.ClinicalTrials.gov) and performed following the Consolidated Standards of Reporting Trials (CONSORT) (SCHULZ et al. 2010). All individuals will be instructed on the procedures and will sign a statement of informed consent. During the study, measures to prevent the spread of the coronavirus will be observed, such as attendance of only one participant per time, use of mask and alcohol gel (COMITÊ PERMANENTE DE ENFRENTAMENTO DO NOVO

CORONAVÍRUS DA UFMG, 2020; MINISTÉRIO DA SAÚDE, 2020).

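### A total of 34 falls just short of the 28 participants required after 20% dropout; it covers 17.6%, and the consequence for power is minor

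*Protocol*

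**What the plan says.** Protocol section 3.6 sizes the trial separately for its two primary outcomes. For inspiratory strength, "thirteen participants per group are required (26 participants"). For expiratory strength, "Considering a significance level ( $\alpha$ ) of 5% and a power of 0.80, fourteen participants per group are required (28 participants"). The larger number is adopted: "Therefore, a sample size of 28 individuals (14 in each group"). The allowance for loss follows: "Assuming an expected dropout rate of 20%, a total sample size of 34 individuals was set (17 in each group").

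The section does not say how 28 became 34. It gives no numerical effect size, standard deviation or sidedness. For the expiratory outcome it says only: "The effect size for expiratory muscle training was also derived from an RCT with a similar population and intervention".

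Two other statements bear on the point. Section 3.0 fixes an "allocation ratio 1:1". Section 3.7 specifies an intention-to-treat analysis and adds: "Data from the last available evaluation will be used for missed sessions".

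**The concern.** A dropout allowance is meant to ensure that, if the expected proportion is lost, the required number remains. The required number must therefore be divided by the proportion expected to stay. Multiplying it by one plus the dropout rate gives too small a total, because the loss applies to the enlarged sample and not to the original one. The total of 34 looks like the product of that second method.

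At stake is whether the sentence is true. It presents 34 as sufficient for 20% loss from a requirement of 28. In a trial with 14 per group, one person is about 7% of an arm's required number (1/14 = 7.1%), so the allowance should be stated correctly even if the error is small.

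**Working it through.** **Inputs, all from protocol sections 3.0 and 3.6**
- Required number: 28 in total, 14 per group (expiratory strength); 26 in total, 13 per group (inspiratory strength)
- Expected dropout: 20%
- Stated total: 34, 17 per group
- Allocation: 1:1
- Significance level 5%, power 0.80

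**1. Reproducing the stated figure**
- N x (1 + d): 28 x 1.2 = 33.6, rounded up to 34
- Per group: 14 x 1.2 = 16.8, rounded up to 17

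Both stated numbers are reproduced.

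**2. The calculation that keeps 28**
- N / (1 - d): 28/0.8 = 35 exactly
- Per group: 14/0.8 = 17.5, rounded up to 18, so 36 in total with equal arms

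No upward rounding of this calculation gives 34.

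**3. What 34 leaves after 20% loss**
- 34 x 0.8 = 27.2 in total, which is 0.8 of a participant below 28
- 17 x 0.8 = 13.6 per group, against 14 required for expiratory strength and 13 for inspiratory strength
- With 36: 36 x 0.8 = 28.8, or 14.4 per group

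**4. What 34 does cover**
- 34 - 28 = 6 losses, and 6/34 = 17.6%
- By arm: 17 - 14 = 3 losses per group, and 3/17 = 17.6%
- A seventh loss (7/34 = 20.6%) leaves 27

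**5. Effect on power for expiratory strength**

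This step rests on assumptions, because the effect size and sidedness are not given. I assume a two-sample t-test at 5% (noncentral t) and a standardised difference d for which 14 per group is the smallest number reaching 0.80. Power is 0.80 with 14 per group at d = 1.100, and with 13 per group at d = 1.145. Any d from 1.100 to just under 1.145 would therefore have produced the stated 14.

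| | Two-sided | One-sided |
|---|---|---|
| Range of d giving 14 per group | 1.100 to 1.145 | 0.965 to 1.004 |
| Power at 14 per group | 0.800 to 0.831 | 0.800 to 0.827 |
| Power at 13.6 per group | 0.788 to 0.819 | 0.789 to 0.816 |
| Power with 13 and 14 completers | 0.784 to 0.815 | 0.786 to 0.813 |

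The entry at 13.6 per group is an interpolation at the expected number of completers; the last row gives the nearest whole-number case. In the two-sided case, power at 13.6 per group reaches 0.80 once d is about 1.118, so it is at or above target over most of the admissible range. At any given d, the loss from 14 to 13.6 per group is about one percentage point (0.800 to 0.788 at the lower end, 0.831 to 0.819 at the upper).

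**The case against.** The strongest objection is that nothing of substance turns on this. The shortfall is 0.8 of a participant and about one point of power. Inspiratory strength needs only 13 per group, so 13.6 still meets its requirement, and only expiratory strength is touched. This stands, and it limits the point to a correction of wording.

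A second objection is that section 3.7 carries the last available evaluation forward, so all 34 randomised participants formally enter the analysis and 13.6 per group is not the planned analysis set. That describes the analysis correctly but does not repair the sentence. Section 3.6 itself enlarges 28 to allow for loss, so its aim is to have 28 left after loss. A carried-forward value also adds no new post-treatment observation; for someone lost before week 8 it is the baseline value.

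Two stronger readings are tempting, and the protocol supports neither. A reader might infer that power falls below 0.80, to about 0.79. That figure arises only if 14 per group gives exactly 0.80. Because 14 is a whole number, the underlying effect size could be somewhat larger, and power at 20% loss could then be as high as 0.82. The 0.79 is the lower end of a range and not an estimate.

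A reader might also treat the chance of retaining 28 as the test. With independent 20% loss that chance is 47% for 34 participants. But the plan states an expected dropout rate and promises no probability of retention. By the same test the correctly inflated 35 succeeds only 60% of the time, so this mainly shows that dropout is random.

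Finally, the multiplication by 1.2 is not stated anywhere. It is a strong inference, since it yields both 34 and 17, but the shortfall does not depend on it.

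**Conclusion.** The point holds as an arithmetic correction of minor consequence. By the protocol's own figures, 34 does not leave 28 after 20% loss, and this part needs no assumption beyond reading the allowance as meant to leave 28. It does not follow that the trial is underpowered. The power range in the working is conditional on a t-test and on 14 being the smallest sufficient group size, and it straddles the 0.80 target. The requirement of 28 itself cannot be checked, because the inputs behind it are not given.

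**What to change.** Reword the last sentence of section 3.6 to say that 34 participants (17 per group) retain 14 per group with up to 3 losses in each, about 17.6%. Do not add a power figure for 20% loss, since the protocol does not give the effect size or sidedness needed to support one. This costs one sentence and no extra participants.

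If the 20% allowance is to stand as written, the matching total is 36 (18 per group), two more participants than now planned.
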